# Comparing mechanochemical endovenous ablation using Flebogrif with endovenous laser ablation in the treatment of primary great saphenous vein incompetence: protocol for a multicentre, open-label, non-inferiority, observer-blinded, randomised controlled trial (REBORN trial)

**DOI:** 10.1136/bmjopen-2024-087490

**Published:** 2024-08-07

**Keywords:** Vascular surgery, Surgical dermatology, VASCULAR SURGERY

## Abstract

**Introduction:**

Endovenous laser ablation (EVLA) is associated with an excellent outcome in the treatment of great saphenous vein (GSV) incompetence. However, the use of thermal ablation requires tumescent anaesthesia and is associated with a risk of thermal damage. Mechanochemical endovenous ablation (MOCA) is a non-thermal ablation (NTA) alternative, which combines mechanical endothelial damage with the infusion of a sclerosant liquid or foam. Tumescent anaesthesia is not required. Preliminary experiences with MOCA using the Clarivein device show less intraprocedural and postprocedural pain and a faster clinical improvement compared with EVLA. Flebogrif (Balton, Poland) is a relatively new MOCA device. To determine the role of MOCA using Flebogrif, a well-designed, randomised controlled clinical trial of sufficient sample size and follow-up time is required. In this article, we provide the study protocol for the REBORN trial, aiming to demonstrate that MOCA using Flebogrif is not inferior to EVLA for the outcome of anatomical success in the treatment of GSV incompetence.

**Methods and analysis:**

This multicentre, open-label, non-inferiority, observer-blinded, randomised controlled trial randomises patients who are diagnosed with GSV incompetence and aged 18–80 years between Flebogrif and EVLA. 310 patients in 3 participating centres (Northwest Clinics Alkmaar, Skin and Vein Clinic Oosterwal Alkmaar and Red Cross Hospital Beverwijk) will be included. The primary outcome is anatomical success at 12 months. Secondary outcomes are intraprocedural pain, operation time, technical success, postprocedural pain, safety, anatomical success during other follow-up moments, complications, clinical success, aesthetic result, disease-specific quality of life, reinterventions, anterior accessory saphenous vein reflux and neovascularisation. Patients will be followed up at 1 week, 1, 6, 12, 24 and 60 month(s) after treatment.

**Ethics and dissemination:**

The institutional review board (Medical Ethical Review Committee of the Vrije Universiteit Medical Center) approved this study on 17 May 2021 under case number 2020.0740. Written informed consent is obtained by the coordinating investigator from all participants prior to study enrolment. After completion of the trial, the results will be submitted to an international scientific journal for peer-reviewed publication.

**Trial registration number:**

Overzicht van Medisch-wetenschappelijk Onderzoek in Nederland, NL-OMON25145, previously NL9527; Centrale Commissie Mensgebonden Onderzoek, NL74491.029.20.

STRENGTHS AND LIMITATIONS OF THIS STUDYThis study is a well-powered randomised controlled trial comparing mechanochemical ablation using Flebogrif with endovenous laser ablation in the treatment of great saphenous vein incompetence.The treatment will be blinded to outcome assessors during follow-up.Patients will be followed up for 5 years.The non-inferiority design does not allow for a superiority comparison.

## Introduction

 Chronic venous insufficiency (CVI) of the lower limbs is a common disorder. The prevalence of superficial vein reflux is 21% in the adult population, which increases linearly with age.^1^ CVI has been associated with decreased general and disease-specific quality of life (QoL).^2^,^4^ CVI is generally caused by insufficiency of the great saphenous vein (GSV).^5^

Minimally invasive endothermal treatment, for example, endovenous laser ablation (EVLA) or radiofrequency ablation (RFA), has become the first line of treatment for superficial venous reflux. This treatment strategy has the advantage of avoiding general anaesthesia, shortening operation time and decreasing postoperative pain and morbidity when compared with open surgery.^6^,^10^ However, the use of endothermal ablation techniques is associated with thermal damage to superficial nerves, skin burn, prolonged pain and the administration of tumescent anaesthesia can also be painful.^11^

Newer treatments modalities, especially non-thermal ablation (NTA) techniques, have potential benefits, such as increased patient acceptability and decreased risk of nerve injury. Currently, there are three NTA techniques that are widely discussed. Ultrasound-guided foam sclerotherapy (UGFS) has been used for some decades and avoids the risk of nerve injury. However, it is not as effective as endothermal ablation. Boersma *et al* reported pooled anatomical success rates of 63.6% after UGFS vs 98.5% and 97.1% after EVLA and RFA, respectively. Short-term clinical success and patient-reported outcome measures were comparable.^12^ Additionally, there is a very rare but well-documented risk of stroke after UGFS.^13^ More recently, two alternative NTA modalities have emerged. The first is cyanoacrylate closure using the VenaSeal Closure System or the VenaBLOCK Venous Closure System. Both devices enable the endovenous delivery of cyanoacrylate tissue adhesive to the vein causing fibrosis. A second alternative is mechanochemical endovenous ablation (MOCA), which combines mechanical endothelial damage with the infusion of a sclerosant liquid or foam. An example is the Clarivein device (Vascular Insights, USA), which combines a rotating wire causing endothelial damage with the injection of a sclerosant solution. The Clarivein device is studied and compared with endovenous thermal techniques in several randomised controlled trials. In both the MARADONA trial and Venefit versus Clarivein trial, pain scores were significantly lower in patients treated with Clarivein.^14 15^ However, these significant differences were not found in other clinical studies.^16 17^ Although overall, anatomical success is higher in patients treated with thermal ablation, similar improvements in clinical scores and QoL scores were found in all studies.^14^,^17^ However, the Clarivein device did not lead to widespread use.

In recent years, a new MOCA device has entered the market; the Flebogrif device (Balton, Poland). The Flebogrif device consists of hooks at the end of the catheter that damage the intima of the vein. This endothelial damage is also combined with the simultaneous injection of a sclerosant foam. No published literature is available that compares treatment using Flebogrif with treatment using Clarivein. The anatomical success rate of Flebogrif ranges from 90% to 96% after a follow-up time of 12 months.^18^,^20^ Iłżecki *et al* reported an anatomical success rate of 92% after 24 months.^21^ Only one study compared Flebogrif with EVLA in a randomised controlled trial, with occlusion rates of 96% vs 98%, respectively.^20^

To determine the role of MOCA using Flebogrif, a well-designed, randomised controlled clinical trial of sufficient sample size and follow-up time is required. The current study has been designed to demonstrate that MOCA using Flebogrif is not inferior to EVLA for the outcome of anatomical success in the treatment of GSV incompetence.

## Methods and analysis

The protocol was drafted in accordance with the Standard Protocol Items: Recommendations for Interventional Trials statements. The trial is registered at ‘Overzicht van Medisch-wetenschappelijk Onderzoek in Nederland, NL-OMON25145’ and ‘Centrale Commissie Mensgebonden Onderzoek, NL74491.029.20’. The trial was previously registered under the reference number NL9527.

### Study design

The REBORN trial is a two-arm, multicentre, open-label, non-inferiority, observer-blinded, randomised controlled trial. Patients with GSV incompetence referred to the Northwest Clinics Alkmaar, Skin and Vein Clinic Oosterwal Alkmaar and Red Cross Hospital Beverwijk will be screened for eligibility by the vascular surgeon or phlebologist in the outpatient clinic. All eligible patients will receive oral information about the study, an information letter and a participant consent form from the vascular surgeon or phlebologist. After receiving written informed consent, the research coordinator ([name]) performs computer randomisation and informs the patients about the treatment group they are allocated to. The intervention group will receive treatment with MOCA using the Flebogrif device. The control group will receive treatment using EVLA. The procedures will be performed by dedicated vascular surgeons. These vascular surgeons are experienced in performing laser therapy treatment, as this is the current standard treatment for GSV incompetence in our practices. Before treating study participants, all vascular surgeons will undergo training and complete a minimum of five supervised Flebogrif treatments to overcome the initial learning curve.

Patients will be followed up at 1 week, 1, 6, 12, 24 and 60 month(s) after treatment. At each follow-up visit, patients will be seen at the outpatient clinic. A window of 4–14 days will be allowed for 1-week follow-up, 4–6 weeks for 1-month follow-up and ±1 month for 6, 12, 24 and 60 months follow-up. A study flow diagram is shown in figure 1, and table 1 shows all procedures and measurements performed at each follow-up visit.

**Table 1 T1:** Study period, procedures and measurements

	Screening	Intervention	1 week	1 month	6 months	12 months	24 months	60 months
Informed consent	X							
Randomisation	X							
Flebogrif/EVLA		X						
Intraprocedural pain		X						
Operation time		X						
Technical success		X						
Postprocedural pain			X					
Safety				X				
DUS*	X	X	X	X	X	X	X	X
Complications		X	X	X	X	X	X	X
VCSS, CEAP	X		X	X	X	X	X	X
Aesthetic score	X		X	X	X	X	X	X
QoL questionnaire	X		X	X	X	X	X	X

* To assess the outcomes of anatomical success, anterior accessory saphenous vein () reflux and neovascularizsation.

CEAP, Clinical Etiology Anatomy Pathophysiology classification; DUS, duplex ultrasound; EVLA, endovenous laser ablation; QoL, quality of life; VCSS, Venous Clinical Severity Score

**Figure 1 F1:**
[figure not shown]
Study flow chart. EVLA, endovenous laser ablation.

### Eligibility criteria

Patients are eligible for inclusion if they fulfil the following criteria:

Age 18–80 years.Unilateral symptomatic primary GSV and saphenofemoral junction (SFJ) incompetence.GSV diameter ≥4 and ≤12 mm.Intrafascial GSV length ≥15 cm.

### Exclusion criteria

Bilateral endovenous thermal/MOCA treatment of the GSV.Simultaneous ipsilateral endovenous thermal/MOCA treatment of additional veins.C6 varicose veins.Previous ipsilateral GSV or anterior accessory saphenous vein (AASV) treatment.Superficial thrombophlebitis or deep venous thrombosis (DVT) in the last 6 months.Occlusion of deep venous system.Coagulation disorders or increased risk of thromboembolism.Use of direct oral anticoagulants or vitamin K antagonists.Pregnancy or lactation.Immobilisation.Cognitive impairment or language barrier.Allergy or contraindication to polidocanol.Severe renal or liver insufficiency.

### Randomisation and blinding

Randomisation will be done by the coordinating investigator. Randomisation to one of two treatment groups will be on a 1:1 ratio. Randomisation will be performed in alternating blocks (4, 6, 8) and stratified on surgeon (n=7), using a web-based randomisation tool: Castor Electronic Data Capture (EDC). Due to the nature of the intervention, it is not possible to conceal the allocation group from either the patients or the treating surgeons. However, the treatment will be blinded to outcome assessors during follow-up as patients are told not to tell which treatment they received.

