#### Anatomical success

The calculation is based on the hypothesis that MOCA using Flebogrif will have no inferior anatomical success 12 months after treatment, compared with EVLA. The anatomical success rate in the EVLA group is expected to be 95%.^22^,^25^ The anatomical success rate in the Flebogrif group is expected to be 93%.^18^,^20^ A non-inferiority margin of −10% is applied. This margin is based on the anatomical success rate of 85% after MOCA using Clarivein.^14 25 26^ Taking into account a power of 80% and a significance level of 2.5% (one-sided test on the lower level of the 95% CI of the expected difference), 278 patients will be needed (https://www.sealedenvelope.com/power/binary-noninferior/). Corrected for 10% lost to follow-up, 155 patients need to be included in each treatment group. The total study population will consist of 310 patients.

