#### Primary outcome analysis

Anatomical success at 12 months of follow-up is a dichotomous variable and will be described as numbers with percentages. The difference between the two groups will be presented as a percentage with a 95% CI. If the lower limit of this CI does not exceed the non-inferiority margin of −10%, the intervention will be considered to be non-inferior. A second analysis will be performed in which data from the last follow-up visit before a reintervention will be used in patients undergoing a reintervention of the GSV after failure of primary treatment.

These analyses will be performed for both the ITT and the PP population. Patients with missing data on the primary outcome parameters will be excluded from analyses.

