#### Secondary outcome analysis

Categorical variables (technical success, safety, anatomical success, complications, clinical success, reinterventions, AASV reflux and neovascularisation) will be described as numbers with percentages. Between-group differences will be analysed using the χ^2^ test or the Fisher’s exact test where appropriate.

Continuous variables that are single measurements (operation time, intraprocedural and postprocedural pain scores) will be described as means with an SD in the case of normally distributed data and as medians with an IQR in the case of a non-normal distribution. Between-group differences will be analysed using the independent samples t-test or the Mann-Whitney U test depending on the data distribution.

Continuous variables that are measured at several moments (VCSS, CEAP Clinical score, aesthetic result and VEINES-QOL/Sym) will be described as means with an SD in the case of normally distributed data and as medians with an IQR in the case of a non-normal distribution. Between-group differences and change over time will be analysed using a linear mixed model. This type of analysis handles missing data well, making imputation unnecessary.

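### Randomisation is stratified by surgeon, but no described analysis uses surgeon; if surgeons differ, some precision is lost, little for the primary outcome and more for operation time and pain

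*Protocol article*

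**What the plan says.** Under Randomisation and blinding, the protocol article states "Randomisation to one of two treatment groups will be on a 1:1 ratio" and "Randomisation will be performed in alternating blocks (4, 6, 8) and stratified on surgeon (n=7". Surgeon is the only stratification factor named.

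Under Primary outcome analysis, the 12-month comparison is described as follows: "The difference between the two groups will be presented as a percentage with a 95% CI". Its lower limit is then compared with the margin. No interval method is named and surgeon is not mentioned.

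Under Secondary outcome analysis, categorical outcomes get a χ² or Fisher's exact test. For operation time and pain scores the text is: "Between-group differences will be analysed using the independent samples t-test or the Mann-Whitney U test depending on the data distribution". Repeatedly measured scores get a linear mixed model whose terms are not listed. Other outcome analysis repeats the same two-sample tests.

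The sample size section assumes "The anatomical success rate in the EVLA group is expected to be 95" per cent and "The anatomical success rate in the Flebogrif group is expected to be 93" per cent, with "A non-inferiority margin of −10% is applied". It uses an online two-proportion calculator, and no surgeon term is mentioned.

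**The concern.** Blocked randomisation within surgeon balances surgeon across the arms, so differences between surgeons largely cancel out of the treatment difference. A test that ignores surgeon still counts those differences in its standard error. If surgeons differ in results, the reported interval is then wider than the design warrants, and the trial does not collect the precision that stratifying made available.

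The χ², Fisher, t and Mann-Whitney tests named for the secondary and other outcomes cannot carry a stratum, so an analysis that follows that text discards the factor. Operation time and intraprocedural pain depend on the operator, and less pain is part of the rationale for the new technique. For the primary outcome, non-inferiority is judged on the interval alone and planned power is 80%, so even a small free gain is worth having.

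**Working it through.** **Plan's own figure.** Inputs from the sample size section: 95% (EVLA), 93% (Flebogrif), margin 10 points, and "a power of 80% and a significance level of 2.5% (one-sided test on the lower level of the 95% CI of the expected difference").

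- Variance sum: 0.95×0.05 + 0.93×0.07 = 0.1126.
- n per arm = (1.960 + 0.842)² × 0.1126 / (0.10 − 0.02)² = 138.1, rounded up to 139; total 278.
- 139 / 0.9 = 154.4, rounded up to 155 per arm; total 310.

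Both figures reproduce with no surgeon term, so the stated power never relied on surgeon adjustment.

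**Unadjusted primary interval at 139 per arm.** SE = √(0.1126/139) = 2.846 points. Half-width = 1.96 × 2.846 = 5.58 points. Power = Φ(8/2.846 − 1.96) = 80.3%.

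**Effect of stratifying.** Let τ be the SD between surgeons of the success probability, assumed equal in both arms and with surgeons of equal size. The article gives no value for τ, so a range is shown.

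- Variance ratio, stratified to unadjusted: 1 − 2τ²/0.1126.
- Power, stratified: Φ(8/SE_s − 1.96), where SE_s = 2.846 × √ratio.
- Power, unadjusted: Φ((8 − 5.58)/SE_s). The unadjusted estimate also varies only within surgeons, but its interval uses the larger SE.

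| τ (points) | Variance ratio | Half-width, stratified | Narrower by | Power, unadjusted | Power, stratified |
|---|---|---|---|---|---|
| 0 | 1.000 | 5.58 | 0% | 80.3% | 80.3% |
| 1 | 0.998 | 5.57 | 0.1% | 80.3% | 80.3% |
| 2 | 0.993 | 5.56 | 0.4% | 80.3% | 80.5% |
| 3 | 0.984 | 5.53 | 0.8% | 80.5% | 80.9% |
| 5 | 0.956 | 5.45 | 2.2% | 80.8% | 82.0% |

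**Simulation check.** Seven surgeons, 20 patients per arm each, 20,000 replicates, Wald intervals, τ from 0 to 5 points.

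- Coverage of the unadjusted interval was 94.6 to 95.1%; that of the stratified interval was nearly the same.
- Mean half-widths, unadjusted against stratified, were 5.50 and 5.52 points at τ = 0, and 5.50 and 5.40 at τ = 5.
- At a true difference of −10 points (95% against 85%), non-inferiority was declared in about 3% of replicates under both analyses. The excess over 2.5% is also present at τ = 0, so it does not come from ignoring surgeon.

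**Continuous outcomes.** If a share ICC of the variance lies between surgeons, the SE ratio is √(1 − ICC), and the equivalent gain in patients is 1/(1 − ICC) − 1. The ICC values are assumptions.

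| ICC | SE ratio | SE lower by | Equivalent extra patients |
|---|---|---|---|
| 0.05 | 0.975 | 2.5% | 5% |
| 0.10 | 0.949 | 5% | 11% |
| 0.20 | 0.894 | 11% | 25% |

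**Stratum size.** With equal caseloads, 310/14 is about 22 patients per arm per surgeon, and 278/14 about 20 evaluable. The chance that such a cell has no failure is 0.95²⁰ = 36% for EVLA and 0.93²⁰ = 23% for Flebogrif, so the stratified interval must cope with strata without failures.

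**The case against.** The strongest reply is that nothing here is invalid. The sample size and an unadjusted analysis agree, and ignoring surgeon is neutral or conservative. The article leaves the primary interval method and the mixed-model terms open, so a stratified risk difference would satisfy its wording, and an unseen analysis plan may specify one. All of this stands. Only the two-sample tests for secondary and other outcomes are actually fixed as unstratified.

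Three stronger readings are tempting, and the documents support none of them.

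- A reader might infer that the intervals are certainly too wide. That holds only if surgeons differ, and no between-surgeon figure is given.
- A reader might take the minimum of five supervised Flebogrif treatments (Study design) as evidence that surgeons differ. Every surgeon meets the same minimum, so it points to a contrast between techniques or a learning curve, not to spread among surgeons.
- A reader might infer that the trial is underpowered or the non-inferiority test too lenient. The reproduced 278 and 310 and the simulation show neither.

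It is also fair to object that a linear model alone would drop the article's provision for non-normal data, which matters for an 11-point pain scale. The fix therefore includes a stratified rank test.

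**Conclusion.** The point holds as one of efficiency and consistency between design and analysis, not as an error of validity. The stratification factor appears in no described analysis, and using it costs nothing in patients.

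For the primary outcome the benefit is small: under 1% of CI width for a between-surgeon SD up to 3 points, and about 2% at 5 points, where power rises by about 1 percentage point (80.8% to 82.0%). It would seldom change a decision against a 10-point margin. For operation time and pain it may be worth having, at 2.5 to 11% of the SE for an ICC of 0.05 to 0.20.

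The direction rests on inference to these seven surgeons with balanced allocation within each. The sizes rest on assumed spreads, equal caseloads and, for the primary outcome, the same spread in both arms.

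**What to change.** State before analysis:

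- **Primary outcome.** Risk difference stratified by randomisation surgeon, with Mantel-Haenszel weights and a stratified score-type interval (for example Miettinen-Nurminen) that tolerates strata without failures. Pool surgeons with very few patients within centre, by a rule set in advance.
- **Operation time and pain.** Linear model with surgeon as a fixed effect or, where data are non-normal, a van Elteren test stratified by surgeon.
- **Repeated scores.** Include surgeon in the linear mixed models.

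The cost is wording in the analysis plan. Surgeon is already recorded in the randomisation system and the sample size need not change. The article names SPSS V.25; check that it produces the chosen stratified interval, and name another package if it does not.

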### Sample size calculation and drop-out

A sample size calculation is performed for the primary outcome of anatomical success at 12 months.

#### Anatomical success

The calculation is based on the hypothesis that MOCA using Flebogrif will have no inferior anatomical success 12 months after treatment, compared with EVLA. The anatomical success rate in the EVLA group is expected to be 95%.^22^,^25^ The anatomical success rate in the Flebogrif group is expected to be 93%.^18^,^20^ A non-inferiority margin of −10% is applied. This margin is based on the anatomical success rate of 85% after MOCA using Clarivein.^14 25 26^ Taking into account a power of 80% and a significance level of 2.5% (one-sided test on the lower level of the 95% CI of the expected difference), 278 patients will be needed (https://www.sealedenvelope.com/power/binary-noninferior/). Corrected for 10% lost to follow-up, 155 patients need to be included in each treatment group. The total study population will consist of 310 patients.

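### At 139 evaluable patients per arm the design does not have both its stated 80% power and its stated 2.5% one-sided error, although the sample size follows correctly from the formula used

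*Protocol article*

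**What the plan says.** All planning inputs are in the protocol article, mostly under Sample size calculation and drop-out, Anatomical success.

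- Control arm: "The anatomical success rate in the EVLA group is expected to be 95" per cent.
- Intervention arm: "The anatomical success rate in the Flebogrif group is expected to be 93" per cent.
- Margin: "A non-inferiority margin of −10% is applied".
- Targets: "Taking into account a power of 80% and a significance level of 2.5" per cent, the latter described as a "one-sided test on the lower level of the 95% CI of the expected difference".
- Result: "278 patients will be needed", raised to 155 per arm and 310 in total for 10% loss. An online calculator is cited.

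Under Randomisation and blinding, "Randomisation to one of two treatment groups will be on a 1:1 ratio", so 278 means 139 evaluable per arm. Under Primary outcome analysis, "The difference between the two groups will be presented as a percentage with a 95% CI", and non-inferiority is judged by its lower limit against −10%. Patients without a primary outcome are left out of the analysis, so with the planned 10% loss the analysed number is about 139 per arm.

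**The concern.** The closed-form calculation treats the estimated difference as normal, with a variance fixed at the planning rates. At 139 per arm, the expected failures are 139 × 0.05 = 6.95 with EVLA and 139 × 0.07 = 9.73 with Flebogrif, about 17 in all. With so few events the estimated variance is itself unstable and is correlated with the estimated difference, so nominal power and nominal error need not be the actual ones.

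In a non-inferiority trial either shortfall matters. Error above 2.5% means more false claims that the new device is acceptable. Power below 80% means a greater chance that a truly non-inferior device fails to show it.

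**Working it through.** **Step 1. Reproduce the plan's figure.** Inputs: control 0.95, intervention 0.93, margin 0.10, one-sided 2.5% (z = 1.960), power 80% (z = 0.842). The distance from the expected difference to the margin is 0.10 − 0.02 = 0.08.

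n per arm = (1.960 + 0.842)² × (0.95 × 0.05 + 0.93 × 0.07) / 0.08² = 138.1, so 139 per arm and 278 in total.

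With 10% loss: 139 / 0.90 = 154.4, so 155 per arm and 310 in total. Both stated totals reproduce. The same approximation gives 80.3% power at 139 per arm.

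**Step 2. Exact operating characteristics at 139 per arm.** For every pair of success counts (x₁, x₀), each from 0 to 139, compute the lower limit of the two-sided 95% interval for the difference and record a pass if it lies above −0.10. Sum the binomial probabilities of the passing pairs:

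P(pass) = Σ Bin(x₁; 139, p₁) × Bin(x₀; 139, p₀).

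Power uses p₁ = 0.93, p₀ = 0.95. One-sided error uses the null point at the planned control rate, p₁ = 0.85, p₀ = 0.95.

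| Interval | Power | One-sided error |
|---|---|---|
| Wald | 79.6% | 3.07% |
| Agresti-Caffo | 78.9% | 2.93% |
| Newcombe | 74.8% | 2.46% |
| Miettinen-Nurminen | 73.4% | 2.29% |
| Wald, continuity-corrected | 73.1% | 2.01% |

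A simulation of 1,000,000 trials agreed with the enumeration. No row meets both targets.

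**Step 3. Does a better test close the gap?** A Neyman-Pearson bound answers this: no test that holds 2.5% along the whole null boundary can exceed about 75.1% power at 139 per arm. The power shortfall is therefore not peculiar to the intervals in the table.

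**Step 4. Dependence on the control rate (139 per arm, true difference −10 points).**

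| Control success | Wald | Newcombe | Miettinen-Nurminen |
|---|---|---|---|
| 90% | 2.76% | 2.58% | 2.38% |
| 95% (planned) | 3.07% | 2.46% | 2.29% |
| 98% | 3.99% | 2.30% | 2.22% |

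**Step 5. If nobody is lost (155 per arm).** Power / error at the design rates: Wald 83.1% / 2.98%; Newcombe 79.6% / 2.56%; Miettinen-Nurminen 77.7% / 2.27%. The bound of Step 3 becomes 79.7%.

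**Step 6. One worked outcome.** Take 7 EVLA and 12 Flebogrif failures among 139 each. The difference is −5/139 = −3.60 points. The Wald lower limit is −3.60 − 1.960 × 3.02 = −9.51 points (pass), Newcombe gives −9.99 (pass) and Miettinen-Nurminen −10.10 (fail).

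**The case against.** The strongest reply is that nothing was miscalculated. The 80% and 2.5% are nominal inputs to a standard approximate formula, the calculator is cited, and the totals follow. A reader might infer from the exact figures that 278 or 310 is an arithmetic mistake or that the trial must be enlarged. The document does not support that: Step 1 reproduces both totals.

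A second reply is that under Wald, the interval matching the formula, power is essentially as stated and the excess error is only about 0.6 points. That is correct and limits the size of the point. The 4.0% Wald error belongs to a 98% control rate, which is not the planning value, and at 90% control the excess is smaller (2.8%). Likewise, 73 to 75% power applies only under a score-type interval, which the article does not specify.

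A third temptation is to fault the article for not naming the interval, or to suggest that the choice will be made after the data are seen. Neither can be counted, because a statistical analysis plan that is not shown may fix it. The interval also moves the verdict little: in the Step 6 example, one failure separates pass from fail.

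What these replies do not remove is the gap itself. Naming an interval settles which of the two figures fails; it does not make both true.

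**Conclusion.** The point stands as one about stated operating characteristics, not about the sample size. With 139 evaluable per arm, 95% versus 93% and a −10% margin, the trial has either about 80% power with about 3.1% one-sided error (Wald), or error held near 2.5% with 73 to 75% power (Miettinen-Nurminen, Newcombe). The discrepancy is about 0.6 points of error or 5 to 7 points of power: modest, but worth correcting because it is cheap to correct. Newcombe holds the error only approximately, reaching about 2.6% at lower control rates. Miettinen-Nurminen stayed below 2.5% at each of the null points tabulated.

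The result assumes independent binomial outcomes, equal evaluable arms, the plan's own success rates and no allowance for stratification by surgeon.

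**What to change.** Under Primary outcome analysis, use the Miettinen-Nurminen score interval for the lower-limit decision. Under Sample size calculation, keep 278 and 310 but restate the power as about 73% with 278 evaluable patients and about 78% if all 310 are evaluable. If Newcombe is preferred, the figures are about 75% and 80%. If Wald is kept, leave the power at about 80% and state that the one-sided error is about 3.1% at the design rates. If the analysis plan already names an interval, only the matching restatement is needed.

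The cost is a change of wording and, under a score-type interval, a less favourable stated power. No additional patients and no change of margin are proposed.
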